### Clinical champion

One FLS clinician at each site will be a ‘Clinical Champion’ [Amendment 02, see
Table 2] to facilitate the implementation of the iFraP intervention. The Clinical Champion’s role will be to promote the iFraP training and use of the iFraP tool locally, mentor iFraP-i clinicians, and act as a link between the FLS team and the Keele University research team. An introduction session with the Keele University research team will outline the Clinical Champion role and responsibilities, with subsequent monthly meetings attended by all Clinical Champions and Keele University research team to share learning, achievements and overcome challenges. To support this role, the Clinical Champion will take part in the iFraP Consultation Skills Training Course and therefore will not deliver FLS NHS usual care (iFraP-u) appointments to avoid contamination. To support implementation of the iFraP training, email reminders and newsletters will also be sent to participating intervention clinicians.

### Data collection

All participants will be asked to complete 3 paper or online (via REDCap) questionnaires, depending on their specified preference. Questionnaires collect data at baseline (before randomisation), 2 weeks and 3 months after FLS consultation.

Case Report Forms (CRFs) will all be completed electronically using REDCap.

**
*Baseline data collection*
**

Baseline data collection will be collected before randomisation, as part of the recruitment pack. Data includes demographic characteristics (date of birth, sex at birth), ethnicity, socioeconomic status (Index of Multiple Deprivation), employment status, marital status, fracture site and risk factors, health literacy
^
25
^, barriers to communication and first language, digital access, experience of osteoporosis medication. Additional measures included are outlined in
Table 1.

**Table 1. T1:** Patient participant questionnaire content.

Trial assessments	Baseline	2-week	3-month
Demographics (date of birth, sex at birth)	✓	✓ *	✓ *
Employment status	✓		
Marital status	✓		
Fracture occurrence including site and date	✓		✓
Fracture risk factors:			
• self-reported height	✓		
• rheumatoid arthritis	✓		
• family history	✓		
• secondary causes see FRAX https://www.sheffield.ac.uk/FRAX/)	✓		
Ethnicity	✓		
Health literacy ^ 25 ^	✓		
Barriers to communication (hearing, vision) and first language	✓		
Digital access	✓		
Experience of osteoporosis medicine	✓		
Socioeconomic status (IMD)	✓		
Beliefs about medicines (BMQ-general) ^ 27 ^	✓		
**Primary outcome**			
Decisional conflict ^ 26 ^		✓	
**Secondary outcome measures for all**			
Modified Patient-Professional Interaction Questionnaire (PPIQ) ^ 28 ^ (see extended data)		✓	
Satisfaction with verbal information ^ 29 ^ and experience		✓	
Recall of, and satisfaction with written information ^ 29 ^			✓
Recall of consultation – including key elements included in the training, being shown the computer, receiving diagnosis, receiving drug recommendation		✓	
Modified Brief Illness Perceptions Questionnaire ^ 30 ^ (see extended data)	✓	✓	✓
Self-reported change in physical activity			✓
Worry about further falls and fractures ^ 31 ^	✓	✓	
Self-perceived fracture risk ^ 32 ^	✓	✓	
Self-reported weight	✓		✓
Alcohol	✓		✓
Smoking	✓		✓
**Secondary outcomes: Recommended medication only**			
Beliefs about medicines (BMQ-specific) ^ 27 ^			✓
Satisfaction with medicines information (SIMS) ^ 33 ^		✓	
Osteoporosis specific values		✓	
Self-reported medicine initiation or intention to initiate		✓	✓
Self-reported adherence ^ 34 ^ and, persistence or discontinuation with medicine			✓
Medicine self-reported side effects	✓		✓
**Health Economic Outcomes**			
Health status – EQ-5D-5L 35	✓	✓	✓
Health care utilisation	✓		✓

*date of birth and sex at birth collected to verify identity at 2 weeks and 3 months

**Table 2. T2:** Protocol amendments since trial registration.

Amendment Number	Protocol Section	Original protocol	Amended details	Date of Amendment REC/HRA approval	Rationale for amendment
AM02 NSA02	iFraP intervention training Patient identification *Nested studies*	Omission of iFraP clinical champion role Patient variables described as ‘sex’ and ‘age’ *[Interviews with primary care clinicians could* *be completed in-person or remotely (by* *telephone or Microsoft Teams)]*	Additional detail about Clinical Champion role included Minor changes to variable names: ‘sex at birth’ and ‘age at invite’, update Trial Manager and timeline *[Primary care clinician interview* *method to remove face-to-face option]*	Dec 2022	To describe FLS Clinical Champion role and clarify patient variables *[The HRA queried the number of GP sites involved* *in the study – this was not possible to predict* *given that the location/site of each primary care* *participant would not be known in-advance.* *Given the geographical spread of potential* *primary care practitioners, interviews were likely* *to be remote.]*
AM04 NSA04	Medical record review *[Nested studies]*	Discontinuation of osteoporosis medicines in medical record review determined by last date of prescription ≥ 6 weeks prior to MRR = yes *[A member of the FLS clinical team to upload* *consultation recording to Keele CTU]* *[Informed consent for face-to-face interviews* *to be gained in-person prior to interview]*	Additional method of identifying discontinuation in medical records: recorded discontinuation in the patient medical record = yes *[An NHS site staff member to upload* *consultation recordings to Keele CTU]* *[Informed consent for face-to-face* *interviews can be obtained in-person* *or remotely prior to interview]*	April 2023	A review of medical records revealed that discontinuation can be explicitly recorded (in addition to only inferring from date prescription filled) *[Greater flexibility required so that NHS research* *teams can support the uploading of consultation* *recordings, where needed.]* *[iFraP-i clinicians can consent to interview and* *consultation recording in one process. Remote* *consent to additional data collection enables* *consultation recordings to begin even if the* *interview has yet to be scheduled.]*
AM07 NSA 07	Patient identification	If a patient provides consent to be contacted, Keele CTU send a study recruitment pack containing the consent form and baseline questionnaire, using their preferred method. If the patient does not return the consent form and/or baseline questionnaire within an agreed time window an FLS appointment will be booked, as per normal NHS care.	A courtesy phone call to be made with patients who consent to be contacted but who do not return the consent form and baseline questionnaire within a defined time window. If the patient cannot be contacted by telephone, they will be sent a reminder postcard.	August 2023	When reviewing recruitment rates, there was evidence that a portion of patients were consenting to contact but not returning the consent form and/or baseline questionnaire. This additional telephone call and/or postcard aimed to improve consent rates.
AM08 NSA 08	Patient identification Follow up assessments	Patient identification: At a mid-point in patient recruitment, the Data Monitoring Committee (DMC) will examine the characteristics of the patients recruited to the trial to determine if the sample is representative of the general population. Dependant on results, NHS sites will be asked to adapt their approach to focus recruitment to underserved groups. Follow up assessments: Non-responders to the 2-week and/or 3 month questionnaires will receive their first reminder after approximately 10 days, as per their contact preference.	Patient identification: Flexibility to consider alternative approaches to recruit underserved groups. Follow up assessments: Non- responders to 2-week and/or 3 month questionnaires, whose preference is for online follow ups, will be sent an additional postal reminder if the follow up questionnaire is not returned.	November 2023	The sample at interim review was 100% self- reported White British. In efforts to address this lack of diversity, an additional FLS site joined the trial (from 3 sites to 4 sites). The FLS was chosen because it served a larger proportion of underserved groups, comparatively to other enrolled FLSs. Wording was changed to allow alternative approaches other than asking NHS sites to adapt their approach to focus recruitment to underserved groups, because it was identified that this may be difficult if ethnicity was not recorded well in medical records. Recruitment and follow up rates were identified as lower than expected. Additional postal reminders for those completing online also aimed to improve follow up rates.
AM09 SA09	Sample size	The original target sample size was 328 patients to achieve 200 patients completing the primary outcome at 2 weeks. Patients will be recruited during an 8-month recruitment period. End of study date = September 2024	The amended target sample size is 380 to achieve 200 patients completing the primary outcome at 2 weeks. Patients will be recruited during an 11-month recruitment period. End of study date = May 2025.	February 2024	The original sample target assumed that approximately 32% of patients would not receive a medicine recommendation (hence for whom the primary outcome is not relevant) and for 10% loss to follow-up in the primary outcome at 2-weeks. Resulting in 200 patients completing the primary outcome. When reviewing recruitment and follow up rates with the DMC and TSC, it was identified that 27% of patients did not receive a medicine recommendation, 20% loss to follow-up in the primary outcome at 2-weeks and for 10% loss due to ‘Do Not Attends’ (DNAs). A target sample of 380 was required to meet 200 responses in the primary outcome.

Amendments related to the process evaluation are provided in
*italics* and square brackets. Amendments 1, 3, 5 and 6 are not included here as they did not have implications for the trial protocol

*
**Primary outcome measure**
*

Patient reported ease in decision-making about osteoporosis medication, collected at 2 weeks, measured using the Decisional Conflict Scale (DCS)
^
26
^. The DSC will be completed by those recommended an osteoporosis medicine, using 16 items each measured using 5 Likert response categories from ‘strongly disagree’ to ‘strongly agree’.

**
*Secondary outcome measures*
**

The secondary outcome measures collected at 2-weeks and/or 3 months following FLS consultation, completed by all participants, include:

patient reported perception of patient centred care at 2 weeks using Patient-Professional Interaction Questionnaire (PPIQ)
^
28
^, modified to i) improve readability, ii) ensure relevance for non-face-to-face consultations, iii) remove binary (he/she) gender pronouns (see extended data)worry about further falls and fractures at 2 weeks
^
31
^
satisfaction with the consultation and general information using the Satisfaction with Cancer Information Profile scale (SCIP)
^
29
^ (modified to refer to ‘osteoporosis’ and ‘bone health’ rather than cancer). Satisfaction with verbal information will be assessed at 2 weeks and satisfaction with written information assessed at 3 months.fracture risk perceptions at 2 weeks
^
32
^
illness perceptions at 2 weeks and 3 months, modified from the Brief Illness Perception Questionnaire
^
30
^ with public contributors to focus on ‘broken bones’ and ‘bone health’ rather than ‘illness’ (see extended data).Self-reported smoking, alcohol, weight and change in physical activity at 3 months.Health related quality of life (EQ-5D-5L
^
35
^) at 2 weeks and 3 monthsrecollection of FLS consultation content at 2 weeks, including key elements of the training in the FLS consultation, whether they received a diagnosis of osteoporosis, or a drug treatment recommendation.healthcare resource use at 3 months, including healthcare professional contacts, medicines and supplements use.

Additional secondary outcome measures will be self-reported at 2 weeks and/or 3 months by participants recommended osteoporosis medication during their FLS consultation. These include:

specific osteoporosis values at 2 weeks, including 5 bespoke questions about the relative perceived importance of osteoporosis medicine benefits (e.g. “how important are these treatment benefits to you e.g. maintaining independence”) and possible side effects and adverse events (e.g. “How likely is it, that you would be put off taking this treatment, because of concerns about e.g. common side-effects with medicines such as indigestion and reflux”) using 5-response categories, from “not at all” to “extremely"satisfaction with Information about Medicine (SIMS)
^
33
^ at 2 weeksbeliefs about medicines (BMQ-specific
^
27
^) at 3 monthsself-reported medicine initiation or intention to initiate at 2 weeks and 3 months and persistence or discontinuation at 3 months.self-reported adherence (Medication Adherence Report Scale
^
34
^) at 3 monthsself-reported medicine side effects at 3 months

Table 1 summarises the content of the participant questionnaires at baseline, 2-weeks, and 3-months.

**
*Follow up assessments*
**

Non-responders to the baseline questionnaire will not be enrolled into the trial and will be allocated a non-trial normal NHS care FLS consultation.

Non-responders to the 2-week and/or 3-month questionnaires will receive a reminder by post and/or email, after approximately 10 days [Amendment 08, see
Table 2]. Non-responders to the reminder will be telephoned (by a blinded trial administrator) after approximately 10 days for MDC. A brief questionnaire for MDC will be sent by post or email to those who cannot be contacted after 3 telephone attempts, as per participant’s preference. The MDC questionnaires aim to collect the primary outcome (if appropriate), health-related quality of life (EQ-5D-5L) and self-reported medicine use, along with date of birth and sex at birth to ensure the data are provided by the intended participant.

The flow of events as participants proceed through the trial is outlined in (
Figure 1) and the timing of key events outlined in
Table 1.

**
*Medical record review*
**

Hospital Medical Record Review (MRR) will be completed 3 months after the FLS appointment. Prescription data, including the number initiated (prescribed osteoporosis drug treatment since FLS date: yes/no) and number discontinued (determined by last date of prescription ≥6 weeks prior to MRR or recorded discontinuation in the patient medical record = yes) will be captured [Amendment 04,
Table 2]. Medical record review will also capture information about appointments/visits related to bone health.

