## Methods

### Trial context

This trial takes place in the context of Fracture Liaison Services (FLSs) in England, UK (sometimes referred to as Fracture ‘Prevention’ Services). FLSs enact secondary fracture prevention by systematically identifying adults aged ≥50 years with fragility fractures and conducting bone health assessments. Services are usually nurse or allied health professional-led and address bone health by assessing the patient's risk of falls and future fracture and providing treatment recommendations to the patient and primary care, at one or more consultations, typically 2 months after the fracture.

Service provision varies across FLSs, with services ranging from operating a ‘one-stop shop’ model of care, meaning that, if appropriate, patients have a bone density scan (Dual-energy X-ray absorptiometry [DXA]), nurse assessment, drug treatment recommendation, and blood tests as part of one consultation. Other FLS models may not complete all components for all patients (for example, not all patients receive a DXA scan), or may split these components across multiple appointments, supported by different communication modalities (remote, face-to-face, letter)
^
22
^.

The trial baseline is taken as the FLS consultation where treatment recommendations are given.

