### Sample size

To address the objectives of the trial, 380 participants (190 in each intervention arm) need to be recruited to detect a between group effect size of at least 0.4 in the primary outcome at 2-week follow-up, with 2-tailed 5% significance and 80% power [Amendment 09, see
Table 2 and progress of the trial]. This sample size target of 380 has been calculated based on estimations that 200 participants will complete the primary outcome at 2 weeks (100 per intervention arm). It is expected that approximately 27% of patients will not receive a medicine recommendation (hence for whom the primary outcome is not relevant), 20% loss to follow-up in the primary outcome at 2-weeks, and 10% loss to follow-up because of ‘Do Not Attends’ (DNAs).

With an estimated standard deviation of 15, this translates to minimum clinically important difference (MCID) of 6 points on the DCS (scale range 0 – 100) – a difference considered to be meaningful and one that produces an effect size in the range of meaningful effect sizes recommended by the authors of the DSC
^
26
^.

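### Follow-up is timed from a consultation that comes after randomisation, so the expected 10% who do not attend have no stated follow-up point for outcomes that could still be collected

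*Protocol article*

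**What the plan says.** All references are to the protocol article.

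- **Order of events.** Under Patient participants and Randomisation, patients consent, return the baseline questionnaire and are randomised. Only then does the site book an appointment with a clinician of the allocated arm. The Baseline data collection section agrees: "Baseline data collection will be collected before randomisation, as part of the recruitment pack".
- **Clock.** Trial context states: "The trial baseline is taken as the FLS consultation where treatment recommendations are given". Trial design, Data collection and Secondary outcome measures place the two questionnaires 2 weeks and 3 months after the consultation. Under Medical record review, "Hospital Medical Record Review (MRR) will be completed 3 months after the FLS appointment", and initiation means a prescription since the FLS date.
- **Non-attendance.** The Sample size section allows for "10% loss to follow-up because of ‘Do Not Attends’ (DNAs". Progress of the trial reports the 10% as observed. No other follow-up date is given for these people.
- **Who should provide data.** Secondary outcome measures assigns EQ-5D-5L and resource use to every participant. Self-reported initiation, persistence and adherence are limited to people recommended a medicine. Access to medical records is part of the main consent, not the optional part.

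**The concern.** Attendance happens after randomisation, and participants know their arm. A follow-up clock that starts only on attendance makes the measured group depend on a post-randomisation event.

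For the DCS nothing can be done, because a person who had no consultation and no recommendation has no decision to rate. Hospital prescribing records, EQ-5D-5L and resource use need no consultation. They inform the second primary objective (cost-effectiveness) and the secondary objective on initiation and discontinuation.

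If sites and the trials unit apply the timing as written, no questionnaire falls due for a non-attender, and arguably no record review does either. An analysis plan can choose an analysis set later, but it cannot recover a questionnaire that was never sent. The comparison for these objectives would then be among attenders, and protected by randomisation only as far as attendance is unrelated to arm.

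**Working it through.** **1. Reproduce the plan's own figures.** The Sample size section gives "With an estimated standard deviation of 15", a "minimum clinically important difference (MCID) of 6 points on the DCS", "with 2-tailed 5% significance and 80% power", 200 completers, and losses of 27% (no recommendation), 20% (2-week loss) and 10% (non-attendance).

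- Per arm: 2 × (1.96 + 0.842)² × (15/6)² = 98.1, so 99. With 100 per arm, power is 80.7%.
- Inflation: 200 / (0.73 × 0.80 × 0.90) = 200 / 0.5256 = 380.5, against the stated "380 participants (190 in each intervention arm) need to be recruited".
- Adding the last two losses instead gives 200 / (0.73 × 0.70) = 391, which does not fit. Non-attendance was therefore applied as its own multiplicative step.

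The target is right and does not depend on this point.

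**2. Number affected.**

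- Non-attenders: 0.10 × 380 = 38, or 19 per arm if equal. Attenders: 342.
- Record review: 342 people if it is tied to attendance, up to 380 if not.
- EQ-5D-5L and resource use, assuming the 20% non-response also applies (the article gives it for the primary outcome only): 380 × 0.90 × 0.80 = 274 without non-attenders. With them, the number is between 274 (none respond) and 380 × 0.80 = 304 (80% respond).

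**3. What unequal attendance would do to record-based initiation.** From the article: 73% recommended a medicine (Sample size) and 75% of those offered one accepting it (Introduction, 25% decline). Initiation among attenders is 0.73 × 0.75 = 54.75%, taken as equal in both arms, so attenders show a difference of 0. Assumed: non-attenders do not initiate, and non-attendance differs by arm around an average of 10%.

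| Non-attendance (assumed) | Initiation, all randomised | Difference |
|---|---|---|
| 10% v 10% | 49.3% v 49.3% | 0 |
| 8% v 12% | 50.4% v 48.2% | 2.2 points |
| 7% v 13% | 0.5475 × 0.93 = 50.9% v 0.5475 × 0.87 = 47.6% | 3.3 points |
| 5% v 15% | 52.0% v 46.5% | 5.5 points |

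If instead attenders initiate at 60% and non-attenders at 10% to 20% (both assumed), 5% v 15% gives 4 to 5 points and 8% v 12% gives 1.6 to 2.0 points.

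**4. Effect of including non-attenders when attendance is equal.** At 10% in each arm and no initiation among them, a true difference among attenders is multiplied by 0.90. For example, 10 points becomes 9.

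**The case against.** The strongest reply is that nothing in the article excludes non-attenders from these outcomes. The 10% appears only in the inflation for the DCS, where the loss is inevitable. EQ-5D-5L and resource use are assigned to every participant. The minimum data collection seeks EQ-5D-5L and medicine use, with the primary outcome only where it applies. The record review counts from the appointment, and a non-attender also had one booked and may be rebooked. Timing follow-up from the consultation is a defensible choice, because it gives both arms equal time after the intervention. The analysis set may be settled in the full protocol, the analysis plan or the separate health economic protocol.

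Much of this stands. Exclusion is an inference from the timing rule, not a stated rule. But the questionnaires are tied to the consultation itself, which a non-attender never has, so assigning them to everyone cannot be carried out as written. Whether the record review date means booked or attended is left open. This concerns data collection, which a later analysis plan cannot repair.

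A reader might infer more, and the article does not support it:

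- **That non-attenders would be imputed at the attenders' initiation rate.** The article only says multiple imputation will be considered, and does not say for whom.
- **That a longer wait in one arm distorts quality-adjusted life-years.** No waiting times are given, and time zero for that analysis belongs to the separate health economic protocol.
- **That the two uses of baseline contradict each other.** Trial design places baseline data before the consultation, so the two can be read together.
- **That self-reported initiation is affected.** It is limited to people recommended a medicine, so non-attenders fall outside it under any clock.

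**Conclusion.** The point holds in a limited form. About 38 of 380 randomised patients are expected to have no defined follow-up point for EQ-5D-5L and resource use, and an ambiguous one for record-based prescribing, although none of these needs attendance. Read literally, the cost-effectiveness and record-based adherence comparisons would rest on attenders.

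Whether this biases anything depends on attendance differing by arm, which the article neither reports nor rules out. Under the assumed splits above, the difference in initiation hidden among attenders runs from 0 (equal attendance) through 3.3 points (7% v 13%) to 5.5 points (5% v 15%). These are illustrations, not estimates. No figure in the article is wrong, and the primary DCS analysis and the target of 380 are untouched. The change is worth making because it is cheap and the questionnaire data cannot be recovered afterwards.

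**What to change.** State the following for randomised patients who do not attend:

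- Follow-up is anchored to the scheduled (first-booked) appointment date.
- The 3-month record review is carried out, counting prescriptions from that date.
- The EQ-5D-5L and resource-use items are sent at the usual intervals from that date.
- They are analysed in their randomised arm for the cost-effectiveness and record-based adherence objectives, with initiation taken from the record and not imputed.
- Attendance, and time from randomisation to consultation, are reported by arm.

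The DCS and the outcomes limited to people recommended a medicine stay as they are. The cost is a few sentences and about 38 extra record reviews and questionnaires. The record reviews fall under consent already given. The downside is a slightly diluted effect on initiation, by a factor of about 0.90 if non-attendance is 10% in both arms and non-attenders do not initiate.

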## Introduction

### Background and rationale

In the UK, three million people are estimated to have osteoporosis
^
1
^, a condition characterised by low bone density, contributing to over 500,000 fragility fractures (fractures resulting from low or no trauma) per year. Evidence-based treatments, such as bisphosphonates, are recommended by the National Institute for Health and Care Excellence (NICE) for people with osteoporosis and/or a high fracture risk
^
2
^. Despite being inexpensive, cost-effective, readily available and effective at reducing fracture risk, 25% of people who are offered medication decline it (non-initiation)
^
3
^. Among those who do start bisphosphonates, few persist for long enough for it to be effective, with persistence estimated at 18% to 75% at one year
^
4
^. Low levels of osteoporosis medicine initiation and persistence, collectively described as ‘adherence’
^
5
^, demonstrates an ‘osteoporosis treatment gap’
^
6
^. The ‘treatment gap’ refers to the proportion of people in whom osteoporosis medicine is recommended by clinical guidelines, but do not receive treatment. The treatment gap arises because people at risk are either not identified or offered treatment, or are offered treatment, but decide not to take it. The newly proposed term ‘care gap’
^
7
^) instead represents the gap between care offered to people with, or at risk of, osteoporotic fractures, and best practice, person-centred care, respecting that non-adherence might represent an informed choice and, instead of focussing on patient non-adherence, shifts attention to interventions and improvements that target healthcare services and professional’s actions and behaviours.

A good quality shared decision-making conversation involves the patient and clinician working together to make decisions based on evidence (including risks, benefits, and possible options) and discussions about how the medicine ‘fits’ with the patient’s life, preferences, beliefs and values
^
8
^. Medicine adherence is optimised if a person believes that a medicine is necessary, relevant, safe, and practicable
^
9
^. This demonstrates how shared decision-making has the potential to support osteoporosis medicine adherence
^
10,
11
^, by ensuring that the medicine is a good ‘fit’ for the patient
^
12

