^. The iFraP intervention is a person-centred consultation intervention, consisting of a computerised individualised DST, clinician training in enhanced shared decision-making, risk communication, health literacy and use of the tool, and additional paper and web-based resources for patients and their primary care provider. We hypothesize that the iFraP intervention will improve patient ease in decision-making about osteoporosis medicines (by increasing the extent that the patient was informed and involved in the consultation), facilitate shared decision-making, increase informed medicine initiation and reduce levels of medicine discontinuation. A protocol outlining the studies that underpinned iFraP intervention development is published
^
20
^, and the results of the development studies are also reported elsewhere
^
17,
21–
23
^.

The current protocol (version 1.6, 13 December 2023) is described below. Key amendments to the protocol since initial trial registration are highlighted with comments in square brackets.

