## Protocol

### Objectives

**
*Primary objectives*
**

The primary objectives of this trial are to determine:

1. the effect of the iFraP intervention on patient reported ease in decision-making about osteoporosis medicines.2. the cost-effectiveness of the iFraP intervention compared to usual Fracture Liaison Services; and the value of acquiring additional information (i.e. value of information (VoI)) on iFraP’s cost-effectiveness.

**
*Secondary objectives*
**

The secondary objectives of this trial are to determine:

3. the effect of the iFraP intervention on a range of patient reported outcomes and experience measures including provision of person-centred care, satisfaction with information, and illness and treatment beliefs.4. the clinical effectiveness of the iFraP intervention on adherence including treatment initiation and discontinuation rates.

Separate protocols will detail the process evaluation and health economic evaluation.

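### The record-review rule for discontinuation ignores days supplied, so it can count persistent patients as stopped and cannot flag late starters by date

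*Protocol article*

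**What the plan says.** The Medical record review subsection of the protocol article sets the timing: "Hospital Medical Record Review (MRR) will be completed 3 months after the FLS appointment". Two prescription outcomes are then defined. The first is the "number initiated (prescribed osteoporosis drug treatment since FLS date: yes/no"), so the first prescription may fall anywhere in the 3 months. The second is the "number discontinued (determined by last date of prescription ≥6 weeks prior to MRR or recorded discontinuation in the patient medical record = yes").

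The Amendment 04 rationale in Table 2 explains that explicit recording of a stop was added "in addition to only inferring from date prescription filled". The date criterion is thus an inference from when a prescription was filled, not from when the supply runs out.

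The measure serves the secondary objective on "the clinical effectiveness of the iFraP intervention on adherence including treatment initiation and discontinuation rates", and the Background states the hypothesis that iFraP will "increase informed medicine initiation and reduce levels of medicine discontinuation". Under Trial context, services are described as "providing treatment recommendations to the patient and primary care". Persistence or discontinuation is also self-reported at 3 months, without any 6-week cut.

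**The concern.** Time since the last prescription shows stopping only if it is compared with how long that prescription lasts. The rule compares it with a fixed 6 weeks, inside a window of about 13 weeks. Two errors follow:

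- **False positives.** A supply or dosing interval longer than 6 weeks can leave the last prescription 6 or more weeks old in someone who has missed nothing.
- **False negatives.** A first prescription after about week 7 is less than 6 weeks old at review, so the date criterion cannot be met even if the patient stops at once.

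The recorded-discontinuation criterion is joined by *or*. It can rescue some false negatives, but it can only add discontinued cases and cannot reverse a false flag.

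At stake is the record-based discontinuation rate, a named part of a secondary objective and the source that does not need a returned questionnaire. It would reflect supply length and start time as well as stopping.

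**Working it through.** The article gives no figure for this rule, so there is none to reproduce. The check applies the rule as written to patients who never stop.

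**Inputs from the article:** review at 3 months, taken as week 13; cut at 6 weeks; first prescription at any time after the appointment.

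**Assumptions:** supply length D weeks (not stated, so a range is shown); refills exactly on time; first prescription at week t, uniform over 0 to 7.

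**Formula:** last prescription = t + D × floor((13 − t)/D). The gap at review is therefore (13 − t) mod D, and the patient is flagged if the gap is 6 or more.

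**Persistent patients wrongly flagged**

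| Supply D | Start weeks flagged | Share of weeks 0–7 |
|---|---|---|
| 6 weeks or less | none, since the gap stays below 6 | 0% |
| 8 weeks | 5 to 7 | 2/7 = 28.6% |
| 12 weeks | 1 to 7 | 6/7 = 85.7% |
| 13 weeks or longer | 0 to 7 | 100% |

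**Check by day.** With review at day 91 and start days 0 to 49 (50 days), a 56-day supply is flagged for starts on days 36–49 (14/50 = 28%), an 84-day supply for days 8–49 (42/50 = 84%), and 112 days or more for all (100%). With review at day 84 the three shares are 33%, 98% and 100%; at day 98 they are 26%, 74% and 100%.

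**Late starters.** If t > 7, then 13 − t < 6, so the date criterion is never met for any D. For example, a patient first prescribed at week 8 who never continues has a gap of 13 − 8 = 5 weeks and is not flagged.

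**Two arms with no true discontinuation in either.** In both scenarios iFraP starts 2 weeks earlier than usual care.

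| Start windows (usual care; iFraP) | Supply | Usual care flagged | iFraP flagged |
|---|---|---|---|
| Weeks 2–10; weeks 0–8 | 8 weeks | 2/8 = 25% | 2/8 = 25% |
| Weeks 2–10; weeks 0–8 | 12 weeks | 5/8 = 62.5% | 6/8 = 75% |
| Weeks 2–10; weeks 0–8 | longer than the window | 5/8 = 62.5% | 7/8 = 87.5% |
| Weeks 2–7; weeks 0–5 | 8 weeks | 2/5 = 40% | 0/5 = 0% |
| Weeks 2–7; weeks 0–5 | 12 weeks | 5/5 = 100% | 4/5 = 80% |

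The same 2-week shift gives no difference, a difference against iFraP or one in its favour, depending on supply length and on whether starts run past week 7.

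**The case against.** **Supply length is unknown.** If every supply is 6 weeks or less and refilled on time, no persistent patient is wrongly flagged. This stands, and the percentages are conditional on it. The missed late starters remain whatever the supply. The article also does not restrict the medicines to one drug or interval; bisphosphonates are only an example.

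**The outcome has other sources.** Discontinuation and adherence are self-reported at 3 months, and minimum data collection seeks self-reported medicine use from non-responders. This limits the damage but does not repair the record-based rate.

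**The article is condensed.** Its list of prescription data is introduced as inclusive, so quantity may already be extracted, and separate analysis plans are to be definitive. That bears on the cost of the change. The rule itself is fixed here and uses no quantity.

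**Stronger readings that the article does not support**

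- *Earlier starters are flagged more often.* The only consistent effect is a step at about week 7, after which nobody is flagged by date. Within weeks 0 to 7 the pattern reverses for 8-week supplies (0% of starts in weeks 0–3.5 against 2/3.5 = 57% in weeks 3.5–7) and for 12-week supplies (2.5/3.5 = 71% against 100%).
- *The rule creates spurious excess discontinuation with iFraP.* The hypothesis is more initiation, not faster initiation, and the two-arm examples show that the sign depends on assumed inputs.
- *GP repeats are invisible to the review.* The review is of hospital records while recommendations go to primary care, but the article does not say whether GP prescribing can be seen there. This is a point to confirm.

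**Conclusion.** The point holds as a defect of measurement. As written, the rule can count fully persistent patients as discontinued when a prescription covers more than 6 weeks, and it cannot detect stopping by date in anyone first prescribed after about week 7. Under the assumptions stated (perfect refills, uniform starts over weeks 0 to 7, review at week 13), the false-flag share runs from 0% at 6 weeks or less, through about 29% at 8 weeks and 86% at 12 weeks, to 100% at 13 weeks or longer. The true share cannot be known without the supply lengths.

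Bias between arms is possible but not shown, in either size or direction. The consequence is confined to one source for a secondary outcome. It merits correction before the data are analysed but does not threaten the trial's main comparison.

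**What to change.** 1. Capture days covered, or the dosing interval, for each prescription in the record review.
2. Define discontinuation as end of supply (prescription date plus days covered) plus one fixed, pre-stated gap falling before the review date, or recorded stopping.
3. Report patients whose supply plus gap has not elapsed by review as not assessable by date, not as persistent, and take their status from 3-month self-reported persistence. Keep all initiators in the denominator: those assessable by date are, by construction, those with a lapse, so a rate among them alone would mean nothing. Show separately those with a repeat on record and those still on their first supply.
4. Confirm that the reviewed record shows GP-issued prescriptions.
5. Keep the 6-week rule as a sensitivity analysis only.

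The cost is one extra extraction field, if quantity is not already captured, and a definition in the protocol and analysis plan. The real downside is that fewer patients can be assessed by date at 3 months. With a 12-week supply and a gap of G weeks, a lapse is visible only if t + 12 + G ≤ 13, that is t ≤ 1 − G. Almost nobody meets this, and for supplies or intervals longer than the window nobody does. The article already accepts that 3 months limits what can be learned about longer-term persistence.
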